#### Subject withdrawal criteria

Study participation will be terminated under the following conditions:

Occurrence of severe complications and/or general health deterioration (i.e., sepsis, bleeding, AV fistula occlusion, and progress of electrolyte disorders such as ECG change of hyperkalemia, or uncontrolled calcium × phosphorus (Ca × P) level);Occurrence of a severe adverse event (AE) of any type during the intervention;Voluntary withdrawal from the trial, absence from two consecutive interviews, or loss to follow-up.

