### Interventions

The CHM product investigated in this study will be prescription-grade JBT powder (Product code; NO.0321131, Ko Da Pharmaceutical Co., Ltd., Taoyuan, Taiwan) manufactured in accordance with Good Manufacturing Practices (GMP) and tested before factory release. Juan Bi Tang consists of 4 g *Rx. Angelica Sinensis*當歸, 4 g *Rx. Paeoniae Rubra*赤芍, 4 g *Rx. Astragali*黃耆, 4 g *Rz. Curcuma Longae*薑黃, 1 g *Rx. et Rz. Notopterygii*羌活, 4 g *Rx. Saposhnikoviae*防風, 3 g *Rz. Zingiberis Recens*生薑, 2 g *Fr. Zizyphi Jujube*大棗, and 1.5 g *Rx. Glycyrrhizae Preparata*炙甘草. These raw herb materials, together with starch excipient, are extracted and concentrated according to a standardized Chinese formula (see: http://www.koda.com.tw/tqm04_e.aspx). The participants will be instructed to take JBT orally in doses of 3 g (per bag) each time, thrice daily, for 4 weeks. Patients will return each week to the outpatient clinic for evaluation, medication, and counting of any unconsumed bags. Weekly compliance below 75% will be considered a deviation from the protocol and will lead to exclusion from further participation in the study. Participants in the non-treatment period will receive simple self-care measures for MPS based on the non-pharmacologic intervention in patients with CKD by Pham et al. (18). These will mainly include physical activities such as stretching, aerobic and strength exercises, and some types of combined exercises (18). The duration of the intervention will be 8 weeks, and the follow-up will be at 2 weeks.

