### Outcome measurement

The subjects will be assessed five times: prior to the study, at 4 weeks (at the end of period I), at 6 weeks (at the beginning of period II), at 10 weeks (at the end of period II), and at follow-up (2 weeks after the trial period ends). A research assistant will be trained to ensure the accuracy of outcome assessments and data collection.

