#### Primary outcome

The primary outcome used in this study will be the Kidney Disease Quality of Life 36-Item Short-Form Survey (KDQOL-36), a self-report measure developed for health-related concerns of individuals who visit dialysis facilities for treatment (29). The KDQOL-36 is available in English and was translated into Mandarin Chinese by the RAND Corporation (see: http://www.rand.org/health/surveys_tools/kdqol.html). The instrument is composed of 12 general health items and 24 kidney-specific items. The items on general health are summarized into a Physical Component Summary (PCS) score and a Mental Component Summary (MCS) score. The 24 kidney-specific items comprise three scales: symptoms and problems, burden of kidney disease, and effects of kidney disease (12, 4, and 8 items, respectively). The raw scores are transformed into a linear range of 0–100, where higher scores indicate better QOL (30).

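### Withdrawal and compliance rules remove patients from the study rather than from JBT, so later KDQOL-36 values are lost and the ITT analysis drifts toward completers

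*Protocol article*

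**What the plan says.** Subject withdrawal criteria opens with "Study participation will be terminated under the following conditions". The listed conditions include "Occurrence of severe complications and/or general health deterioration", "Occurrence of a severe adverse event (AE) of any type during the intervention" and "absence from two consecutive interviews", alongside voluntary withdrawal and loss to follow-up.

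Interventions sets the dose "in doses of 3 g (per bag) each time, thrice daily, for 4 weeks", has unused bags counted at weekly visits, and adds: "Weekly compliance below 75% will be considered a deviation from the protocol and will lead to exclusion from further participation in the study".

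Outcome measurement and Table 1 schedule KDQOL-36, the primary outcome, at weeks 0, 4, 6, 10 and 12. It is "a self-report measure developed for health-related concerns of individuals who visit dialysis facilities for treatment", so completing it does not depend on taking JBT.

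Safety assessments follows adverse events until the patient recovers. No section continues KDQOL-36 after removal. Data analyses promises both ITT and PP analyses, with repeated measures ANOVA, and GEE where normality fails. The Discussion falls back on first-period data alone if carry-over is found.

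**The concern.** Both rules end participation in the study, not just treatment. Followed as written, they stop primary outcome collection after randomisation in patients whose health worsened or who did not keep taking JBT. Missingness of that kind is unlikely to be random.

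Excluding poor compliers is a per-protocol criterion. Applied to data collection, it pulls the ITT set toward the PP set. This does not formally contradict the promised ITT analysis, but it weakens it.

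The loss is also tied to treatment. Compliance is counted in bags, so that rule cannot act in a no-treatment period. If more patients leave on JBT than off it, and those who leave are doing worse, the remaining data flatter JBT. Removal before week 4 also takes away the value that the first-period fallback needs. Repeated measures ANOVA in its usual form drops incomplete patients. GEE keeps the available visits but does not correct informative missingness. A separate SAP could add missing-data methods, but it could not recover values that were never collected.

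**Working it through.** **The plan's own figure.** Sample size states 34 evaluable and 40 recruited. Take 25% as Cohen's f = 0.25, with two groups, m = 2 measurements, alpha 0.05 and a correlation of 0.5 (assumed; not stated). The noncentrality is f² × N × m / (1 − 0.5) = 0.0625 × 34 × 2 / 0.5 = 8.5, giving power 0.807 at N = 34. Then 34 / 0.85 = 40. Both figures reproduce, and the allowance covers 40 × 0.15 = 6 losses.

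**Compliance threshold.** 3 bags × 7 days = 21 a week. 16/21 = 76.2% passes and 15/21 = 71.4% fails. Six missed bags, or two days of doses, in any one week remove the patient.

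**KDQOL-36 visits lost (schedule: weeks 0, 4, 6, 10, 12).**

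| Removed | Visits lost | Share |
|---|---|---|
| Before week 4 | 4, 6, 10, 12 | 4 of 5 |
| In the washout | 6, 10, 12 | 3 of 5 |
| Period II, before week 10 | 10, 12 | 2 of 5 |

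No row leaves both end-of-period values (weeks 4 and 10). The compliance rule acts in period I for group A (4 of 5 lost) and in period II for group B (2 of 5 lost), so the loss is uneven by sequence.

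**Bias.** The document gives no termination rates, so the inputs here are assumptions. Let pJ and pC be the termination rates on and off JBT, s the score deficit of terminated patients in SD, r the share of a period I deficit that persists to week 10, and tau the effect in patients without an event.

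- Group A, JBT minus control, all data: tau − pJ·s·(1 − r) + pC·s.
- Group B, JBT minus control, all data: tau − pJ·s + pC·s·(1 − r).
- Average of the two: tau − (1 − r/2)(pJ − pC)s.
- Completers give tau, so the bias is (1 − r/2)(pJ − pC)s.
- The first-period comparison has bias (pJ − pC)s whatever r is.

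With s from 0.5 to 1 SD:

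| Excess on JBT | Within patient, r = 0 | Within patient, r = 1 | First period |
|---|---|---|---|
| 0 | 0 | 0 | 0 |
| 1 in 40 | 0.013–0.025 | 0.006–0.013 | 0.013–0.025 |
| 2 in 40 | 0.025–0.05 | 0.013–0.025 | 0.025–0.05 |
| 4 in 40 | 0.05–0.10 | 0.025–0.05 | 0.05–0.10 |

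A simulation with tau = 0.5, correlation 0.5, pJ = 0.10, pC = 0 and s = 1 gave the same bias for completers and for exchangeable GEE on available visits: 0.10 SD (r = 0) and 0.05 SD (r = 1).

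**A second illustration.** Suppose there is no true effect and a fraction q of patients is removed on JBT only, selected on a latent score with correlation c to the outcome. The JBT mean shifts by c × φ(z)/(1 − q), where z is the normal quantile at q. At q = 0.10 the factor is 0.1755/0.90 = 0.195, so c = 0.3 to 0.7 gives 0.06 to 0.14 SD. At q = 0.20 it is 0.280/0.80 = 0.350, giving 0.105 to 0.245 SD. With c = 0 there is no shift.

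**Precision.** If the chance of falling below 75% is p per JBT week, four-week removal is 1 − (1 − p)⁴. For p = 1%, 2% and 5% (assumed) this is 3.9%, 7.8% and 18.5%. On top of the 15% allowance, 40 × 0.85 × (1 − 0.078) = 31.4 patients remain at p = 2%, below the required 34. On the same inputs, power is 0.753 at 30 patients and 0.869 if all 40 contribute.

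**The case against.** The strongest reply is that the bias is not demonstrated. Nothing in the document shows more clinical terminations on JBT than off it, and Safety assessments reports no major toxicity in earlier studies. With equal rates the bias from these terminations is zero. A patient who misses two days of bags may simply have forgotten, may be burdened by many medicines, or may feel better, and then there is no deficit to lose. This stands: direction and size are both assumed. Against it, the document itself names bleeding and hyperkalemia both as reasons for termination and as severe events that could be related to JBT, so an excess on JBT is plausible.

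The figures are also small beside the trial's noise. At a correlation of 0.5 and 34 patients, the within-patient standard error is about 1/√34 = 0.17 SD. For 17 against 17 in period I it is √(2/17) = 0.34 SD. The extreme 0.10 SD is about 0.6 and 0.3 of these. The trial also calls itself a pilot. This limits the grade of the concern but does not remove it, because bias does not average out and the remedy is cheap.

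The simulated GEE result follows from its set-up: a deficit that is never observed cannot be recovered from observed visits. It illustrates the point and is not evidence about this trial.

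Two side points are hypothetical. A patient whose JBT is held for an adverse event could fail the bag count, but the article describes no dose hold. A patient in hospital could miss two interviews, but that term is not defined.

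Finally, that KDQOL-36 stops on removal is inferred from a condensed article. It is the plain meaning of both rules, and nothing in the article contradicts it.

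**Conclusion.** The concern holds. Both rules end study participation, no section keeps KDQOL-36 going, and the ITT analysis is compromised by losses that, for the compliance rule, can arise only on JBT. The data loss follows directly from the text. The size of the bias does not: it rests on assumed termination rates, an assumed deficit of 0.5 to 1 SD and an assumed degree of persistence. Under those assumptions it runs from zero (equal rates) to 0.10 SD in favour of JBT (an excess of 4 in 40 with a 1 SD deficit). The 15% allowance offsets part of the lost precision and none of the bias. The plan should be changed, but the point is not fatal to the trial.

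**What to change.** Reword Subject withdrawal criteria and the compliance sentence in Interventions together:

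1. The clinical criteria stop or withhold JBT only.
2. Weekly compliance below 75% is a protocol deviation that excludes the patient from the PP set only. It does not apply where JBT was stopped or withheld for safety.
3. Visits missed because of such an event do not by themselves end participation.
4. Unless consent is withdrawn, KDQOL-36 and other feasible outcomes continue at the remaining scheduled visits.
5. A group B patient with an event in period I starts JBT in period II only if the investigator judges it safe. Otherwise JBT is withheld and outcomes are still collected.
6. All these values enter the ITT set by randomised sequence, and the week 4 first-period comparison is reported beside the within-patient contrast.

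Voluntary withdrawal and loss to follow-up still end participation.

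The planned 40 does not change. The direct cost is protocol wording and a few self-report questionnaires at visits already scheduled. There are two statistical costs. First, the ITT effect is diluted by k/40 if k patients take no JBT: 2.5%, 5% or 10% for 1, 2 or 4. The PP analysis still shows the result in patients treated as planned. Second, a period I event whose effect lasts to week 10 partly cancels in the within-patient contrast, so some harm on JBT is charged to the no-treatment period (about half with full persistence and equal event rates in the two periods). The first-period comparison avoids this but is less precise, which is why both should be reported.

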### Interventions

The CHM product investigated in this study will be prescription-grade JBT powder (Product code; NO.0321131, Ko Da Pharmaceutical Co., Ltd., Taoyuan, Taiwan) manufactured in accordance with Good Manufacturing Practices (GMP) and tested before factory release. Juan Bi Tang consists of 4 g *Rx. Angelica Sinensis*當歸, 4 g *Rx. Paeoniae Rubra*赤芍, 4 g *Rx. Astragali*黃耆, 4 g *Rz. Curcuma Longae*薑黃, 1 g *Rx. et Rz. Notopterygii*羌活, 4 g *Rx. Saposhnikoviae*防風, 3 g *Rz. Zingiberis Recens*生薑, 2 g *Fr. Zizyphi Jujube*大棗, and 1.5 g *Rx. Glycyrrhizae Preparata*炙甘草. These raw herb materials, together with starch excipient, are extracted and concentrated according to a standardized Chinese formula (see: http://www.koda.com.tw/tqm04_e.aspx). The participants will be instructed to take JBT orally in doses of 3 g (per bag) each time, thrice daily, for 4 weeks. Patients will return each week to the outpatient clinic for evaluation, medication, and counting of any unconsumed bags. Weekly compliance below 75% will be considered a deviation from the protocol and will lead to exclusion from further participation in the study. Participants in the non-treatment period will receive simple self-care measures for MPS based on the non-pharmacologic intervention in patients with CKD by Pham et al. (18). These will mainly include physical activities such as stretching, aerobic and strength exercises, and some types of combined exercises (18). The duration of the intervention will be 8 weeks, and the follow-up will be at 2 weeks.

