### Statistical analysis

#### Sample size

A statistical power analysis by G^*^Power version 3.1.9.2 for the differences in the outcome measure between both groups was conducted to determine the investigated sample size to achieve adequate power (80%, α = 0.05). For repeated measures ANOVA analysis, to achieve 80% power and a 25% effect size (40), at least 34 participants will be needed. Considering a 15% loss to follow-up, we plan to recruit 40 participants (20 participants for each group) to compensate for possible dropouts.

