#### Data analyses

Both intention-to-treat (ITT) and per-protocol (PP) analyses will be applied in the present trial. Continuous data will be presented as mean ± SD, and categorical data will be presented as frequencies and proportions. The Student's *t*-test for continuous variables and chi-squared test for categorical variables will be used to compare the characteristics and clinical data of patients with and without JBT treatment. Repeated measures ANOVA will be conducted to compare the subjects' conditions over time. The Mann–Whitney U test and generalized estimating equation will be applied to compare differences when the distribution of data does not meet the assumption of normality. All analyses will be performed in IBM SPSS Statistics 22 (IBM Co., Armonk, NY, USA). A *p*-value <0.05 will be considered statistically significant.

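### Low JBT compliance ends study participation rather than only per-protocol status, so the promised ITT analysis would depend on outcomes that are never collected

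*Protocol article*

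**What the plan says.** The compliance rule stands in the Interventions section of the protocol article: "Weekly compliance below 75% will be considered a deviation from the protocol and will lead to exclusion from further participation in the study". The same section gives the only way in which compliance is measured: "Patients will return each week to the outpatient clinic for evaluation, medication, and counting of any unconsumed bags". The unit counted is the JBT bag, taken in "doses of 3 g (per bag) each time, thrice daily, for 4 weeks". The comparator has no bags and no adherence threshold: "Participants in the non-treatment period will receive simple self-care measures for MPS".

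Data analyses then promises two analysis sets: "Both intention-to-treat (ITT) and per-protocol (PP) analyses will be applied in the present trial". The method for change over time is: "Repeated measures ANOVA will be conducted to compare the subjects' conditions over time". Generalized estimating equations are named for data that are not normally distributed.

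Subject withdrawal criteria has its own list, introduced by "Study participation will be terminated under the following conditions". It covers severe complications, severe adverse events, voluntary withdrawal, missed interviews and loss to follow-up. Low compliance is not on it. Sample size allows for attrition with "Considering a 15% loss to follow-up".

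**The concern.** An ITT analysis needs outcomes from every randomised patient, whether or not treatment was taken as planned. Here the protocol itself stops follow-up of patients because they did not take the treatment. The wording removes them from the study, and not merely from JBT or from the per-protocol set. Nothing in the article says that they go on attending outcome visits.

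The rule is also one-sided. Since the only compliance measure is the bag count, a patient can fail it only while on JBT. Missingness is therefore tied to treatment, and in an open-label trial with a patient-reported primary outcome it may also be tied to perceived response.

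At stake is the question that the Discussion sets for the trial, namely whether JBT is preferable to non-pharmacologic measures. Patients who cannot keep up the regimen are part of that answer. If their later outcomes are missing, the ITT result moves towards the effect in those who complied.

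**Working it through.** **1. The plan's own figure.** Inputs from Sample size: effect size 25% (taken as f = 0.25), α = 0.05, power 80%, two groups. Assumed, because not stated: two measurements (m = 2), correlation ρ = 0.5, sphericity. For the within-subject or interaction test, λ = f²·N·m/(1−ρ) = 0.0625 × 34 × 2/0.5 = 8.5 with 1 and 32 degrees of freedom. Power is 0.807, and 34 is the smallest even N that reaches 80%. Then 34/(1−0.15) = 40. Both planned figures reproduce, and the allowance is 6 of 40 patients.

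**2. What triggers exclusion.** Three bags a day for seven days is 21 bags. 0.75 × 21 = 15.75, so six or more missed bags put a week below the threshold.

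**3. How many could be excluded.** The document gives no compliance rate, so the weekly failure risk p is assumed. If one failing week is enough and weeks are independent, the share excluded over the course is 1−(1−p)⁴:

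| Weekly risk p | Excluded over 4 weeks | Of 40 |
|---|---|---|
| 2% | 7.8% | 3.1 |
| 4% | 15.1% | 6.0 |
| 5% | 18.5% | 7.4 |
| 10% | 34.4% | 13.8 |

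The allowance is used up by this rule alone at p = 1−0.85^(1/4) = 4.0% per week. On the assumptions of step 1, power is 0.869 with 40 completers, 0.807 with 34, 0.753 with 30 and 0.721 with 28.

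**4. Which outcomes are lost.** Assessments are at weeks 0, 4, 6, 10 and 12 (Table 1; Outcome measurement).
- Group A takes JBT in period I. A patient excluded before week 4 can lose the week-4 JBT endpoint and all of period II. One excluded at a week-4 bag count may still have the week-4 outcome but loses period II.
- Group B takes JBT in period II. An excluded patient keeps weeks 0, 4 and 6, which is the whole control period, and can lose week 10. If the last bag count is made at the week-10 visit, a failure in the final week costs only week 12. In that case the endpoint is lost with probability 1−(1−p)³, which at p = 4% is 1−0.96³ = 11.5%.

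With equal groups, the loss of complete within-patient comparisons at p = 4% is then about (15.1% + 11.5%)/2 = 13.3%, slightly under the allowance.

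**5. What this can do to the estimate (illustrative).** Suppose that JBT has an effect of 0.50 SD in compliers and none in a fraction q who are excluded. Complete pairs estimate 0.50 SD, while the all-randomised effect is 0.50 × (1−q):
- q = 5%: 0.475 SD
- q = 10%: 0.45 SD
- q = 15%: 0.425 SD
- q = 25%: 0.375 SD

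**6. The period-I fallback.** The Discussion says that, if carry-over appears, only first-period data will be used, as a parallel-group comparison. Group A compliers would then be compared with all of group B. With no true effect, and an assumed prognosis 0.5 SD worse in non-compliers, the group A mean rises relative to group B by 0.5 × q. That is 0.025 SD at q = 5% and 0.125 SD at q = 25%.

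**The case against.** Several objections have force, and they limit the point.

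- **ITT is not impossible.** A reader might infer that it cannot be done, or that it becomes identical to the per-protocol analysis. The document does not support that. Data before exclusion remain, generalized estimating equations can use incomplete records, and an unseen SAP may specify a missing-data method. What stands is that no SAP can recover outcomes that were never collected, so any such analysis leans on assumptions that the data cannot test.
- **The trigger is open to reading.** The rule refers to weekly compliance without saying that any single week suffices. If an average over the course is meant, the four-week formula does not apply. The rule's absence from the withdrawal list adds to the doubt.
- **Direction of bias.** A reader might infer that the result must favour JBT. Patients who find JBT ineffective or hard to tolerate may well skip bags, but patients whose pain has resolved may too. Within complete pairs, moreover, compliers are compared with themselves, so 0.50 SD is a valid figure for a different population.
- **Safety.** A reader might infer that safety results are biased as well. Safety assessments provides for adverse events to be followed until recovery and for severe JBT-related events to be reported within 24 hours. At most, some later scheduled laboratory or adverse-event visits could be lost.
- **Pilot status.** The trial calls itself a pilot, and every failure rate and effect size in steps 3, 5 and 6 is assumed. This bears on how much weight the numbers carry. It does not remove the conflict between the rule and the promised analysis.

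**Conclusion.** The point holds as a conflict between a stated rule and a stated analysis. The exclusion rule stops outcome collection selectively under JBT, is missing from the formal withdrawal list, and undercuts the promised ITT analysis by pushing it towards compliers. The loss is uneven between sequences, and in the period-I fallback it would break the randomised comparison.

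The size is not known. Under the one-failing-week reading, a weekly failure risk of about 4% would use the whole 15% allowance, 2% would use about half, and 10% would exceed it twofold. Bias in favour of JBT is plausible, but neither its size nor its direction can be established from the document. The conclusion rests on two readings: that bag counting is the only compliance measure, and that exclusion from further participation means no further outcome visits. Both follow from the text as it stands.

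**What to change.** Reconcile Interventions, Subject withdrawal criteria and Data analyses:

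- Let compliance below 75% remove a patient from the per-protocol set only, and state whether one week or the course average counts for that purpose.
- Keep collecting all remaining scheduled outcomes (weeks 4, 6, 10 and 12) for every randomised patient, unless consent is withdrawn or the patient is truly lost to follow-up.
- In the withdrawal criteria, separate the ending of study treatment from the ending of data collection.
- Analyse all randomised patients by assigned sequence.

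Whether a patient with low compliance continues JBT is a clinical decision and is not addressed here.

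The cost is a short amendment and some extra follow-up, in patients who already attend dialysis three times a week. The ITT estimate may turn out less favourable.
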